### Sample size

Target sample size calculations are based on the primary aim and outcome of the study evaluating mean differences between different treatment cohorts. This was conducted for hypothesis testing against minimal clinically significant difference (MCSD) of the five mental wellbeing measures of interest, as previously reported in the literature. This was calculated utilising a one-way ANOVA across the four cohorts. Common standard deviation (SD) derived from the literature, or previous pilot data from a small cross-sectional sample were also used to subsequently calculate the effect size f value, with a power of 0.8 and an alpha value of 0.05 utilised. G*Power Software V3.1 [30] was used to calculate the required sample sizes. The largest required sample size across the five mental wellbeing measures was used as the required minimal sample size.

PHQ-9 –MCSD of 5 [31], SD of 3.49 (pilot data)GAD 7 –MCSD of 5 [32], SD of 3.49 (pilot data)FCR7 –MCSD of 10, SD 7.01 [24]BIS–No clear MCSD published in literature [33], use of 10 as cut off for significant symptoms [25], SD of 3.93 (pilot data)Masculine Self-Esteem MCSD of 9.8 [34], SD of 15.79 [35]

Sample size calculations utilising the above values revealed a maximum requirement of 232 participants (58 per cohort) using the PC-QOL Masculine Self-Esteem Scale. Assuming a reasonable dropout rate of 25%, a requirement of 75 participants per cohort was set to give an overall target sample of 300 participants. During recruitment, individual treatment cohorts of these sizes will be targeted, with a gradual stop in recruitment across these different cohorts to gain sizes of groups as close to equal as possible. However, due to likely unequal dropout rates and some crossover to different treatment arms during follow up (e.g. those undergoing surveillance subsequently undergoing radical treatment) it is likely some disparity in cohort sizes will exist. These would subsequently require consideration within analysis and conclusions drawn from study results if any individual cohort contains fewer than the minimum sample size described above.

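### Minor arithmetic error: a target of 300 (75 per cohort) leaves 225, not the required 232, at the stated 25% dropout

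*Protocol article*

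**What the plan says.** All the relevant figures stand in the Sample size section of the protocol article.

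- **Method:** a one-way ANOVA across four cohorts, "with a power of 0.8 and an alpha value of 0.05 utilised". A calculation was made for each of the five mental wellbeing measures.
- **Minimum:** "The largest required sample size across the five mental wellbeing measures was used as the required minimal sample size". The calculations "revealed a maximum requirement of 232 participants (58 per cohort) using the PC-QOL Masculine Self-Esteem Scale".
- **Target:** "Assuming a reasonable dropout rate of 25%, a requirement of 75 participants per cohort was set to give an overall target sample of 300 participants".
- **Use of the minimum later on:** recruitment aims for near-equal cohorts, but unequal dropout and crossover between treatments are expected to produce some disparity. This is to be considered in the analysis and conclusions "if any individual cohort contains fewer than the minimum sample size described above".

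The Statistical analysis section adds that multiple imputation will be considered for missing outcomes where possible, with complete case analysis otherwise.

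**The concern.** The section links three numbers: a minimum of 58 per cohort, a dropout rate of 25%, and a target of 75 per cohort chosen to absorb that dropout. They cannot all hold. If exactly the assumed proportion is lost, evenly across cohorts, every cohort ends slightly below the minimum.

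Two things depend on this. The first is the power statement for the primary outcome, which should be true under its own dropout assumption. The second is the role of 58 as a working threshold. The text attributes cohorts below it to unequal dropout and crossover, and does not tell the reader that the planned target already falls under it on average at the planned dropout rate.

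**Working it through.** **Inputs, all from the Sample size section:** alpha 0.05; power 0.80; k = 4 cohorts of equal size; masculine self-esteem difference 9.8 and SD 15.79; minimum 232 (58 per cohort); dropout 25%; target 300 (75 per cohort).

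**Step 1. Reproduce 232.** The standardised difference is d = 9.8/15.79 = 0.6206. The article does not state the pattern of the four means, so several were tried. With two cohorts d apart and the other two midway, f = d × √(1/8) = 0.2194. Power is taken from the noncentral F distribution with 3 and N − 4 degrees of freedom and noncentrality N × f².

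| Pattern of means | f | Required N (per cohort) | Power at 232 | Power at 225 |
|---|---|---|---|---|
| Two extremes, two midway | 0.2194 | 232 (58) | 0.803 | 0.789 |
| Equally spaced | 0.2313 | 208 (52) | 0.847 | 0.834 |
| One cohort differs | 0.2687 | 156 (39) | 0.941 | 0.934 |
| Two against two | 0.3103 | 120 (30) | 0.985 | 0.982 |

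The first pattern is the least favourable of the four and gives the article's figure exactly. The 232 is therefore accepted.

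**Step 2. Apply the stated dropout to the target.**

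- Total: 300 × (1 − 0.25) = 225, which is 232 − 225 = 7 short.
- Per cohort: 75 × 0.75 = 56.25, which is 58 − 56.25 = 1.75 short.

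**Step 3. Inflate the minimum correctly, n/(1 − dropout).**

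- Per cohort: 58/0.75 = 77.3, so 78, and 4 × 78 = 312.
- Total: 232/0.75 = 309.3, so 310.
- Check: 312 × 0.75 = 234, which is at least 232.

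**Step 4. Find the dropout that 300 does cover.** 1 − 232/300 = 0.227, which is 17 losses in each cohort of 75.

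**Step 5. A possible origin of 75.** Multiplying by 1.25 instead of dividing by 0.75 gives 58 × 1.25 = 72.5, so 73 per cohort, which could have been rounded up to 75. The article does not say so, and that method would not retain 58 after a 25% loss either.

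**Step 6. Size of the effect.** For masculine self-esteem under the first pattern, power falls from 0.803 at 232 to 0.789 at 225 (0.787 at 4 × 56 = 224). For the other measures, the article's differences and SDs with the same pattern require only 48 in total for PHQ-9, GAD-7 (same inputs as PHQ-9) and FCR7, and 20 for BIS. Their power at 225 exceeds 0.999.

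**The case against.** The strongest reply is that very little turns on this. The gap is 7 of 232 participants and about one percentage point of power, on one of five measures. Even that loss depends on a pattern of means inferred from the result: with equally spaced means, power at 225 is 0.834. All of this stands, and it is why the point is minor.

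Two further replies carry less weight. The section does allow for undersized cohorts, but it attributes them to unequal dropout and crossover, not to the target itself. Multiple imputation might mean that more than the complete cases are analysed, but it is only to be considered, and the 75 was set expressly to absorb dropout. Neither makes 75 × 0.75 reach 58.

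A reader might also draw two stronger conclusions that the documents do not support.

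- **That the study is seriously underpowered.** It is not: four of the five measures keep power above 99% on the article's own inputs, and the fifth loses about a point.
- **That this error is what makes cohorts below 58 likely.** Mostly it is not. If each participant dropped out independently at 25% (an assumption the article does not make), a correctly inflated cohort of 78 would keep at least 58 with probability of only about 0.61, and all four cohorts would do so with probability of about 0.14. Chance variation around the threshold would often trigger the caveat even with the right target.

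**Conclusion.** The recruitment target is wrong as written, and the error is minor. That 225 is below 232, and 56.25 below 58, follows from the article's own figures and does not depend on any pattern of means. The statement about power does: about 79% against the stated 80% applies to masculine self-esteem only, at exactly 25% dropout with equal cohorts, under the least favourable pattern that reproduces 232. The reason to correct it is that the sample size statement for the primary outcome should agree with its own inputs; the loss of power alone would not demand it.

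**What to change.** Keep the target of 300 and restate the sentence on dropout, for example:

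> 300 participants (75 per cohort) retain the required 232 (58 per cohort) if dropout is at most about 22%; at 25% dropout about 225 (56 per cohort) remain and power for masculine self-esteem is about 79%.

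Leave the under-size threshold at 58 per cohort. It agrees with the power calculation, and lowering it to 56 would relax a pre-stated criterion to fit the shortfall.

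The cost is one sentence and a slightly less favourable power figure. Raising the target to 312 would also restore consistency. However, the Study design and setting section has recruitment starting in January 2021 and the last participant finishing in Spring/Summer 2023 after 12 months of follow-up, so that may no longer be practical, and a one-point loss of power does not call for it.

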### Data storage and retention

All data is handled in accordance with current legislation, including General Data Protection Regulation (GDPR) and the Data Protection Act 2018. All data collected either digitally or physically is subsequently digitally stored in secure encrypted storage devices with password protected access. Physical data collected such as postal questionnaires is stored in locked file cabinets in areas with limited access. All digital data is pseudonymised with any identifiable data required for study conduct stored separately with only essential central research team having access to these. The study chief investigator (KA) acts as the overall responsible data controller for the study duration.

Following study completion all identifiable information will be destroyed following one year, once dissemination of results to participants has been completed. Subsequent storage of fully anonymised data and metadata arising from the study will be archived on the King’s College research depository for a minimum of 20 years and made publicly available through a unique DOI post publication of results. Express written consent for this long-term storage is sought from participants during recruitment.

### Ethics approval and safety considerations

The study abides by the principles of the Declaration of Helsinki with the study protocol and associated study documents receiving full prospective National Health Service (NHS) ethics committee and Human Research Authority (HRA) approval on 9^th^ November 2020 (NHS REC Reference: 20/LO/1136). Additionally, local institutional approval at each individual study site was gained prior to initiation of recruitment. MIND-P is also registered on ClinicalTrials.gov (NCT04647474).

While this observational study is low risk, questionnaires completed by participants cover sensitive topics around mental health, of which some cannot ethically be ignored if issues are identified. These include concerns surrounding severe depression, anxiety, and suicidal ideation. Whilst expected to be rare in the study population a protocol has been put into place to ensure issues of concern are appropriately reviewed by a relevant healthcare professional (Fig 3). Those with less severe symptoms will receive relevant information on where self-help can be gained and encouraged to self-refer to the general practitioner or local Improving Access to Psychological Therapies (IAPT) services. However, for more severe symptoms direct referral to the usual care team or the participants general practitioner is made. Participants are made aware of this requirement during the consenting process. Furthermore, within the study website links to well recognised information and help sources are provided, including official NHS websites, a link to the Samaritans website and a link to identify local IAPT services.

**Fig 3 pone.0284727.g003:**
[figure not shown]
Decision tree for referral requirement post questionnaire completion.

### Patient and public involvement (PPI)

Patient involvement was actively sought during the design of the study through its presentation at the South East London Consumer Research Panel for Cancer (SELCRP) at Guy’s Cancer centre, with a panel of 15 cancer patients. Feedback was sought on suitability and importance of research question, study design, consenting methods and patient burden of the study. Feedback received demonstrated the research question to be relevant and of high importance to the quality of life of cancer patients. The study burden was deemed small in view of minimal time requirement and ability to complete the questionnaires at home. Therefore, it was viewed patient involvement would overall benefit future cancer care. The telephone consenting method was an acceptable method for delivery of information, with virtual forms acceptable for those with access. The primary concern for study methodology, included accessibility and inclusivity of all patients for the remote study design. This was subsequently addressed by ensuring the availability of different methods of completion of the follow up questionnaires, either via postal or email links. Additionally, participants and the public will form part of the dissemination strategy. Participants will be informed of the study results on publication of results, with findings openly available on the study website and disseminated through social media.

## Discussion

MIND-P is a prospective cohort study that aims to primarily evaluate prognostic factors for mental wellbeing outcomes in newly diagnosed prostate cancer patients in the initial follow-up period. With the current paucity of data available for prognostic factors in these outcomes within a prostate cancer population, this study will mainly serve as an exploratory study to further identify potential patient, oncological and treatment factors of interest. These findings will be of importance by identifying factors that should subsequently be specifically evaluated in further prospective studies within different settings to identify their individual prognostic value [19]. Additionally, these findings will be of use when considering future prognostic model research within the field, helping to identify candidate predictor variables and limit the number of variables which are evaluated within an individual model [20]. Lastly, findings will be of use clinically. Not only may they highlight the prevalence of mental wellbeing issues in prostate cancer, but also could help identify individuals who may be at increased risk of developing issues, and thereby highlighting those who require additional monitoring or support.

Strengths of this study include its prospective longitudinal design with much of the existing literature evaluating these outcomes within cancer being largely cross-sectional. Additionally, unlike many studies, we are seeking to evaluate multiple relevant mental wellbeing outcomes, which were selected as important outcomes to prostate cancer patients through extensive background work. Thereby, this allows for a more holistic evaluation of mental wellbeing, rather than overly focused on pure mental health outcomes or specific individual constructs. However, as with any study potential limitations exist. Firstly, the observational methodology means that factors evaluated cannot be subsequently causally attributed to outcomes of interest. However, with the aim being to evaluate prognostic factors rather than causal evaluation this may not necessarily hinder study results. Additionally, whilst employing a multi-institutional design across multiple settings, findings for this study remain within the UK context and are limited to the recruited treatment groups with those undergoing chemotherapy or HIFU excluded. Lastly, the study is primarily powered for detecting differences between treatment cohorts meaning that findings for remaining patient and oncological factors should still be considered exploratory.

Dissemination of subsequent study results is aimed across several platforms. Firstly, presentation at local, national, and international meetings across urological, oncological, and psychological settings is planned. Additionally, final findings will be published within a peer-reviewed urology or oncology journal. Findings will also subsequently be distributed through social media of authors and the study website to ensure as widespread dissemination as possible. Lastly, findings will be directly distributed to participants as per the study PPI plan.
